This paper describes the research protocol for an evaluation of a Street Crisis Response Team (SCRT) in San Francisco, California, a model that tailors its services to PEH. Mental illness and substance use disorders are highly prevalent among adult PEH in San Francisco, yet access to appropriately tailored services is limited. Especially troubling is the inequity of the burden of these diagnoses within this population: a third of PEH in San Francisco identify as Black/African American, compared to 5% of the overall population. Across the US, people with serious mental illness comprise approximately one quarter of all PEH, and up to one third has a substance use disorder [2], with people of color dramatically over-represented in this population [11]. Despite these trends, engaging PEH in mental health and substance use care as well as social services is impeded by marginalization, dehumanization, and structural violence, which interfere with trust and engagement in health care and social services [12].

We will employ an implementation science approach to study a novel mobile crisis program by drawing on empirical data from the health care system as well as perspectives from service recipients, which will allow for a deeper understanding of the utility—and potential limitations—of measuring traditional service outcomes in this setting [13]. We anticipate that this study will yield findings that inform both the implementation of existing, and the planning and evaluation of future mobile crisis programs.

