### Program

The Behavioral Health Services division of the San Francisco Department of Public Health (SFDPH) has an extensive infrastructure for mental health and substance use disorder services, yet one important gap has remained: real-time response for people in behavioral health crisis in the streets. In 2019, San Francisco’s 9-1-1 call data indicates that approximately 50,000 behavioral health related calls were received, most of which were responded to by a law enforcement unit. Because most calls were not related to criminal events, and instead to mental health and social needs experienced by PEH, San Francisco behavioral health and governmental leaders worked with community stakeholders to create the SCRT to respond as an alternative able to be more responsive to behavioral health crises that happen on the street [16].

The SCRT was designed based on previous co-responder models [17, 18]. To meet the goal of diverting calls that would typically go to the San Francisco Police Department, this trauma-informed specialty behavioral health team is dispatched solely by 9-1-1 operators. The SCRT utilizes a co-responder model comprised of a behavioral health clinician, a paramedic from the San Francisco Fire Department and a peer specialist. Each team member plays a role in providing care including immediate stabilization of urgent medical need (paramedic), de-escalation of the crisis (behavioral health clinician) and person-centered peer support (peer specialist). The team triages clients to the appropriate level of care, be it through resolution of the crisis in the field, linkage to outpatient mental health and substance use services, or transport to an acute treatment setting. The SCRT was first piloted in San Francisco’s highest demand neighborhoods in December 2020 and then was incrementally expanded to be citywide by June 2021 (Fig 1).

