#### Study population

The SCRT aims to provide specialty mental health response and enhanced resources to adults in San Francisco who experience crises related to mental health and/or substance use disorders and are experiencing homelessness. Therefore, the study population will be defined based on age greater than 18 years, meeting criteria for homelessness in the 12 months prior to or 3 months following the crisis episode, and receipt of crisis care from any of San Francisco’s “front door” programs for people in an acute behavioral health crisis. These settings include two mobile crisis programs (Comprehensive Crisis Services and the SCRT), a crisis stabilization unit (DORE Urgent Care Clinic), and emergency psychiatric services (Zuckerberg San Francisco General Hospital’s Psychiatric Emergency Services [PES] and Emergency Department visits with a primary behavioral health diagnosis) (Fig 2). The population of housed adults utilizing acute behavioral health services will be utilized as a control group in the ITS sensitivity analyses.

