**Fig 2 pone.0295178.g002:**
[figure not shown]
System map of crisis system entry points in San Francisco used for defining index crisis episodes. MC–mobile crisis; CF–crisis facility; ED–emergency department; SCRT–Street Crisis Response Team; CCS–Comprehensive Crisis Services (adult/child mobile crisis team in San Francisco); DUCC–DORE Urgent Care Center; ZSFG ED–Zuckerberg San Francisco General Hospital Emergency Department; PES–Psychiatric Emergency Services. ‡—ZSFG ED limited to medical episodes with primary ICD-10 diagnosis of mental health, substance use, or suicide Z-codes.

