This analysis will use several design and analysis strategies to account for potential threats to internal validity. First, the study design using two nonequivalent groups with staggered implementation (crisis episodes with zip codes corresponding to neighborhoods that did or did not have the SCRT active during the partial implementation phase prior to citywide expansion) will allow for a between-site comparison of the pilot catchment area relative to the non-pilot areas (Fig 1). Additional sub-analyses will examine within-site differences for the pilot neighborhoods across the three time periods, and, separately, within-site differences for the non-pilot neighborhoods. Second, a non-equivalent non-treatment control group (non-homeless adults accessing crisis services) will be compared to the target population (homeless adults accessing crisis services) using a difference of differences approach to account for secular variations in mental health and substance use service utilization. Third, a series of non-equivalent dependent outcome variables that are not expected to be impacted by the implementation of the SCRT (e.g., non-crisis initiation of outpatient mental health services) will be evaluated across the same time periods with a similar goal of accounting for secular variations in mental health service utilization. Additional issues such as autocorrelation of repeated measures on individuals will be corrected for in the final analyses.

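### The non-treatment control for the difference-in-differences is defined by housing status alone and may contain SCRT recipients, so a null contrast cannot by itself be put down to secular change

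*Protocol article*

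**What the plan says.** The section on the interrupted time series (ITS) analysis lists three safeguards for internal validity. The second is a difference-in-differences in which "a non-equivalent non-treatment control group (non-homeless adults accessing crisis services) will be compared to the target population"; its purpose is to remove secular variation in service use. The Study population section gives the same group a supporting role: "The population of housed adults utilizing acute behavioral health services will be utilized as a control group in the ITS sensitivity analyses".

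Four other places bear on whether that group is untreated:

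- **Study population**, on the crisis programs through which people enter: "These settings include two mobile crisis programs (Comprehensive Crisis Services and the SCRT), a crisis stabilization unit". This list sits in the definition of the homeless study population. For the control, the article refers only to acute or crisis services in general.
- **Fig 2 caption**: "System map of crisis system entry points in San Francisco used for defining index crisis episodes". The map includes SCRT and is not split by housing status.
- **Program**: "this trauma-informed specialty behavioral health team is dispatched solely by 9-1-1 operators". No housing criterion for dispatch is given.
- **Introduction**: SCRT is "a model that tailors its services to PEH". This states an orientation, not an eligibility rule.

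Homelessness is established from records: "meeting criteria for homelessness in the 12 months prior to or 3 months following the crisis episode". According to the Covariates section, it is shown by use of a service that signals unstable housing or by self-report during health care. No section excludes, counts or adjusts for SCRT recipients in the housed group.

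**The concern.** A non-treatment control should be free of the intervention by construction. This one is not. An adult seen by SCRT who has no qualifying homelessness record is an adult accessing crisis services, and as written would fall in the control and be counted as untreated from December 2020 on. Any SCRT effect in such people is then subtracted from the effect in people experiencing homelessness (PEH).

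The contrast is only a sensitivity analysis, but readers are likely to lean on it. The pilot versus non-pilot comparison has unserved areas only until citywide expansion, so in the full-implementation period (August 2021 to August 2022) housed adults are the only concurrent comparison group named. The Limitations section warns that incomplete location data may impede location-specific analysis, and that COVID effects cannot be fully accounted for. A null difference-in-differences could then be taken to show that secular change explains any improvement seen in PEH, when exposure in the control could produce the same result.

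**Working it through.** The article gives no SCRT share by housing status, no effect size and no sample size, so there is no figure of its own to reproduce. The check is bias algebra over assumed ranges.

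**Inputs (all assumed)**
- t = share of PEH episodes with SCRT contact; c = the same share for housed episodes.
- d_h, d_c = effect per contact in PEH and in housed adults.
- Parallel secular trends, and SCRT acting only through contact.

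**Formula**
- Effect in the target population = t × d_h.
- Difference-in-differences = t × d_h - c × d_c.
- Fraction recovered = 1 - (c/t) × (d_c/d_h).

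**Equal effects (d_c = d_h)**: the fraction recovered is 1 - c/t = (t - c)/t.
- t = 30%, c = 5%: 25/30 = 83%.
- t = 30%, c = 10%: 20/30 = 67%.
- t = 30%, c = 15%: 15/30 = 50%.
- t = 20%, c = 10%: 10/20 = 50%.

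**Fraction recovered when the effects differ**

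| d_c/d_h | c/t = 0.10 | c/t = 0.25 | c/t = 0.50 | c/t = 1.00 |
|---|---|---|---|---|
| 1 | 0.90 | 0.75 | 0.50 | 0.00 |
| 0.5 | 0.95 | 0.875 | 0.75 | 0.50 |
| 0 | 1.00 | 1.00 | 1.00 | 1.00 |
| -0.5 | 1.05 | 1.125 | 1.25 | 1.50 |

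The size depends on the ratio c/t, and the direction on the sign of d_c/d_h.

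**A second reason not to presume the direction.** Homelessness can be recorded up to 3 months after the episode and at health care contacts, so SCRT contact might itself move people from the control to the target group. Take 1000 truly homeless adults (outcome 30%) and 1000 housed adults (45%), with no SCRT effect. With 20% of the homeless unrecorded, the control rate is (450 + 60)/1200 = 42.5%. If that share falls to 10%, the rate is (450 + 30)/1100 = 43.6%; at 0% it is 45.0%. The target group stays at 30%, so the contrast is -1.1 or -2.5 points with no true effect. With the two outcome rates swapped it is +1.1 or +2.5 points. These inputs are also assumed.

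**The case against.** The strongest reply is that nothing in the article shows that any housed adult received SCRT. The program was built around the needs of PEH, and the list of crisis settings that names SCRT belongs to the PEH definition. The wide homelessness window should move many SCRT contacts out of the control, which makes a large c less plausible. The group is already labelled non-equivalent, it serves sensitivity analyses only, and two other safeguards do not depend on it. The planned crisis-trajectory variable could show the exposure, and the handling of exposed controls might be left to an analysis plan that is not shown.

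Much of this stands. A reader might infer that part of the control is treated and that the contrast therefore underestimates the effect. The article does not support that: it gives no housed share of SCRT contacts and no effect in housed recipients. Nor does it support carrying the point over to the main single-group ITS, which does not use the housed group, or to housing assessment, which is defined only among PEH.

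The mismatch between label and definition does not go away. The article itself calls the group untreated while defining it in a way that can admit SCRT recipients, so this is not merely detail deferred elsewhere. An aim to serve PEH is not a bar on others, and a homeless recipient without a qualifying record would also land in the control. The trajectory variable makes measurement possible, but the article does not tie it to this contrast.

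**Conclusion.** The point holds in a conditional form. The control is not shown to be untreated. If it contains SCRT recipients and SCRT acts in the same direction in them, the contrast loses a fraction c/t of the true effect under equal per-contact effects, for example 10% at c/t = 0.10 and 50% at c/t = 0.50. The loss is smaller if the effect in housed adults is smaller, nil if there is none, and turns into overstatement if it is opposite. All of this assumes parallel trends and an effect that works only through contact. The true c and t are unknown from the article, so the size is unknown too.

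The consequence is confined to this sensitivity contrast, for routine care, crisis reutilization and jail entry. There it matters for interpretation: until housed exposure is shown to be negligible, a null contrast cannot separate secular change from exposure in the control.

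**What to change.** 1. Call the group a lower-exposure comparison group instead of a non-treatment control.
2. Tabulate, for each of the three study periods, the share of PEH episodes and of housed episodes with any SCRT contact, using the trajectory variable planned in the Index crisis episode section.
3. Add a sensitivity analysis that leaves out housed episodes with SCRT contact. State that this selects on something that can happen only after launch and so changes who is in the control; it should stay secondary.
4. State that a null contrast will not be read as secular change alone unless the table shows negligible housed exposure.
5. Treat any rescaling by the exposure difference as exploratory, because it assumes equal effects in the two groups and no effect other than through recorded contact. It is not needed for the main message.

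A further sensitivity analysis that fixes homelessness status from pre-episode records would address the reclassification question.

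The cost is a few sentences, one table and one or two extra model runs on data already planned for extraction.

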#### Equity analysis

We will conduct additional ITS analyses of each model by stratifying the population by our covariate on race and ethnicity (defined by patient self-report in EHR demographic records). By stratifying the total population into sub-categories of interest, including ethnoracial groups, and comparing the outcomes of the ITS analyses, we will be able to describe whether the potential impact of the SCRT intervention was equitably distributed across racial groups [28–31]. Furthermore, we will be able to identify if potential baseline disparities are perpetuated or reduced by implementation of the SCRT, as has been described in the RE-AIM model [32, 33].

### Qualitative design

To identify individual, community and societal-level factors associated with optimal and suboptimal implementation of the SCRT from a client perspective, semi-structured interviews will be conducted with recipients of the SCRT and post-crisis outreach services. Qualitative data will be analyzed using a thematic analysis approach and further support interpretation of the quantitative findings.

#### Interview participant recruitment and consent

Our study team will partner with the post-SCRT outreach clinicians to engage with individuals who received SCRT services to help recruit a sample purposively selected based on receipt of services and the quantitative post-crisis routine care and reutilization outcomes. Potential participants will be eligible if they received SCRT services 7 to 90 days prior to contact with the study team, to provide time for the resolution of their recent crisis while limiting potential effects of recall bias. During post-crisis follow-up, OCC clinicians will describe the study and, for those interested, document consent for our team to contact them and to review their medical records. Those who consent to be contacted by the research team will have the option to provide their contact information (i.e., phone number, email address) for the research team to identify and contact them for recruitment purposes. Potential participants will also be recruited directly using various methods, such as circulating flyers in areas that frequently serve PEH (e.g., shelters, social service organizations, and on SCRT units themselves). We will then contact prospective participants and arrange to meet participants in person or speak by telephone. Consent will be obtained immediately prior to the interview. Verbal consent procedures were approved by the UCSF Committee on Human Subjects Research to allow for telephonic interviews; written consent was also obtained for in-person interviews. A $60 gift card incentive will be offered to all participants upon completion of the interview. Community stakeholders will be engaged to provide additional suggestions about recruitment strategies.

#### Semi-Structured Interviews

Questions for the semi-structured interviews will be developed *a priori* based on examination of the literature, our team’s clinical experience with crisis services, and feedback from the SCRT team and community stakeholders. The 30- to 60-minute interview will include specific questions about baseline engagement in health care and housing systems, SCRT’s accessibility, SCRT intervention and assessment, post-crisis linkage to care, and overall client experience. Open-ended questions and follow-up prompts will aim to elicit the participant’s perception of the encounter and SCRT’s role in their broader experiences of homelessness, mental illness and substance use. All interviews will be conducted by teams of two researchers, audio recorded and transcribed for qualitative analysis using Atlas.ti Version 9 software.

#### Qualitative coding and analysis

The interview findings will be coded for salient themes using a grounded theory approach [34]. An initial codebook will be developed based on the interview guide, prior literature and overall study goals, and then during the analysis will allow for new codes and themes to emerge organically from the text [35]. Our research team will meet weekly about emerging themes and to discuss iterative changes to the codebook until group consensus determines that saturation has been reached [36]. Finally, we will examine codes and discuss possible models that help organize the themes, such as Bronfebrenner’s Socio-ecological Model [37].

### Mixed methods analysis

Once both the ITS and qualitative analyses have been completed, the results of each will be examined in conjunction with the other to assist with interpretation of the overall study findings. For example, measuring quantitative service utilization outcomes among interview participants can help inform how we interpret their reports of how SCRT impacted their lives. If the equity analyses produce concerning signals for disparities in care, we could incorporate this information into how we analyze qualitative findings about discrimination. Another example would be if we find a lack of significant change in the ITS analysis of post-crisis routine care utilization after implementation of SCRT, in which case our interpretation may be informed by qualitative descriptions of barriers to accessing routine care. These kinds of mixed methods approaches allow us to leverage the nuanced details of qualitative research and the more representative findings in population-level quantitative research to arrive at a stronger set of interpretations and conclusions.

## Discussion

Many states and counties throughout the U.S. have turned to mobile crisis services as a potential cost-effective solution to constraints in behavioral health service capacity. A 2020 report issued by the Substance Abuse and Mental Health Services Administration, titled “National Guidelines for Crisis Care–A Best Practice Toolkit,” lays out essential services for a crisis continuum of care: call centers, mobile teams, and stabilization centers [38]. Programs such as SCRT are key to health systems seeking solutions to divert 9-1-1 calls away from law enforcement and instead to specialized behavioral health clinicians who can triage and link clients to an appropriate level of care. Further implementation science research is essential to grow the evidence base for effective mobile crisis models to help address the behavioral health needs of people experiencing a crisis, especially vulnerable populations such as people experiencing homelessness and health disparities.

The study described in this protocol exemplifies how implementation science methods can increase our understanding of the effectiveness and acceptability of mobile crisis response programs. By describing factors and mechanisms that facilitate or impede the effectiveness of SCRT in diverting clients from unnecessary additional crisis services or jail entry while improving linkage to routine care and housing services, this study will inform future strategies for implementing mobile crisis interventions into other settings. Additionally, the qualitative approaches will provide a nuanced understanding of how an intervention such as SCRT impacts the lives of adults experiencing homelessness in San Francisco and allow for more refined interpretation of the quantitative findings.

### Limitations

There are several limitations to the research methods described above. While ITS designs can measure the impact of a non-randomized intervention, this quasi-experimental approach may not yield definitive results and may be specific to San Francisco and therefore less generalizable to other regions. The electronic records used to describe health, housing and jail service utilization does not capture all services provided in settings outside of the San Francisco Department of Public Health. Though data from 9-1-1 dispatch might help identify which cases are being diverted from SFPD to the SCRT, these data will not be available for this evaluation. It is not possible to fully account for the potential impacts of COVID on data collection and service utilization. Incomplete data on the location of PEH may impede any location-specific analysis; in this case, only the pre-pilot and full implementation segments would be included in the ITS. Limitations in the semi-structured interviews may include sampling bias that results from recruitment through the clinical program, the difficulty of locating potential participants, and the need to exclude potential participants who do not have capacity to consent due to psychiatric or other symptoms; recall bias related to traumatic experiences while in crisis; and desirability bias due to difficulty describing negative experiences of the health care system.

## Conclusion

Studying the implementation of this novel mobile crisis service model will take a step toward increasing our understanding and uncovering mechanisms of impact associated with these widely utilized yet under-evaluated programs. As mobile crisis programs are introduced across the U.S., we aim to provide a model for how mixed-methods evaluations can be achieved in real-world program crisis service settings as a way to advance the literature in this important health services area.
